## Abstract

**Background:**

Childhood overweight and obesity is a significant public health issue. A key contributing factor is sugar sweetened beverages (SSBs) consumption. Evidence suggests that secondary school students are frequent consumers of SSBs, with high daily consumption. The promotion of water consumption and provision of chilled water stations can reduce SSBs consumption. The *Thirsty Choose Water!* study will evaluate the effectiveness of two interventions, a behavioural intervention, *Thirsty? Choose Water!* behavioural intervention (TCW-BI), that target students through the domains of the health promoting high schools framework, and the second intervention is the installation and promotion of chilled water stations.

**Methods/design:**

This community trial will recruit 60 secondary schools from across three Local Health Districts (LHDs) within New South Wales (NSW). A two-by-two factorial study design will be used to determine the effect of the *Thirsty? Choose Water!* behavioural intervention (TCW-BI), and the installation of chilled water stations. The recruited secondary schools will be randomised and non-blinded to one of four study arms receiving either the TCW-BI or chilled water stations, both interventions, or neither (control group). Baseline measures will be collected including student self-report surveys which will gather data regarding knowledge, attitudes and consumption of water and SSBs, a school profile and an environmental scan. Student surveys will be repeated post the intervention and at follow-up. Regular water meter readings will determine the water flow from the chilled water stations across the study period.

**Discussion:**

There is an increasing body of evidence which suggests that decreasing consumption of SSBs can impact positively on childhood overweight and obesity. However, in the Australian context there are limited studies on how this may occur in the secondary school setting. This study will add to this evidence base and establish the effectiveness of TCW-BI and chilled water stations, either alone or combination on increasing water consumption in adolescents. Information about barriers and facilitators to implementation will be documented. Packages to support the implementation of the TCW-BI as a state-wide initiative will be developed.

**Trial registration:**

Australian and New Zealand Clinical Trials Register ACTRN12618000526279 April 2018.

**Electronic supplementary material:**

The online version of this article (10.1186/s12889-018-5685-1) contains supplementary material, which is available to authorized users.

## Background

### Childhood overweight and obesity

Childhood obesity is a serious public health challenge in Australia, with approximately one in four (27.4%) children aged 5–17 years being overweight or obese [1]. Compared to healthy weight range children, those above a healthy weight are more likely to develop chronic conditions including asthma, Type 2 diabetes, poor emotional wellbeing, poor academic performance [2] and to become obese adults [3].

Compelling evidence suggests sugar sweetened beverages (SSBs) are detrimental to health and contribute to obesity [4]. Recent systematic reviews confirm the link between SSBs consumption and weight gain in both children and adults [5, 6], and that reducing SSBs consumption reduces weight gain in children, particularly in those who are already overweight [7]. During adolescence SSBs consumption increases, with nearly 25% of NSW children aged 12–17 years consuming SSBs at least 5 or more times per week [8]. Substitution of SSBs with water has been associated with a reduction in BMI in early adolescence and increasing the consumption of water has been shown to decrease the incidence of overweight/obesity in children [9]. At a population level, reducing consumption of SSBs is an important modifiable behaviour to address and in combination with other strategies can contribute to alleviating the problem of overweightness and obesity.

There is increasing evidence that addressing this issue in the school setting has merit. A recent systematic review [10] examined 36 interventions in school settings that targeted the individual, the environment or both. This review demonstrated that 70% of these interventions were effective in decreasing SSB consumption, with effectiveness increasing for those interventions that targeted legislation or the environment. Moreover, a systematic review of educational and behavioural interventions to reduce SSB consumption in children and adolescents, found the trend toward reduction in SSB consumption approached statistical significance in those studies conducted within school-based settings (*p* = .06) [11].

Other evidence suggests school based education programs promoting increased water consumption can impact positively on SSBs consumption [12] as can the provision of chilled water stations and water bottles [13] which has been shown to increase water consumption in children and decrease the incidence of overweight in children [13–15].

In view of this evidence, interventions using the health promoting schools framework to address SSB consumption holds promise, and is the basis of this study intervention. A recent Cochrane systematic review demonstrated modest positive intervention effects on range of health indicators for interventions that utilised the Health Promoting Schools Framework [16].

This study is an expansion of an initial pilot project conducted on the NSW Central Coast. In 2016 Central Coast Local Health District piloted a component of the *Thirsty? Choose Water!* behavioural intervention (TCW-BI) targeting the partnership domain of the Health Promoting Schools Framework. Partnering with immunisation nurses, the post-immunisation waiting period was used to deliver messages that promoted water as a preferred drink, and generate discussion regarding SSBs. All year 7 students involved in the secondary school immunisation program were exposed to the intervention. Post-immunisation nurses directed students to participate in “Spouts and Straws” (snakes and ladders), a game which introduces messages about the benefits of water consumption and the negative health effects of SSBs. Preliminary findings suggested students’ knowledge and awareness regarding SSBs increased, with some changes in their water drinking habits. The evaluation indicated high levels of acceptability for students, teachers and immunisation staff and utilising the immunisation program as an opportunity to deliver health messages was considered practical and effective.

This current study expands on this pilot, examining the impact of a TCW-BI addressing all aspects of the health promoting schools framework and/or the installation of chilled water stations on Year 7 secondary school students’ knowledge, attitudes and behaviours regarding the consumption of SSBs and water.

## Methods/design

### Aim

The research aim is to determine if the TCW-BI and/or the provision of chilled water stations increases water consumption in year 7 secondary students and effect changes in students’ knowledge, attitudes and behaviour regarding SSBs.

### Study design

A two-by-two factorial design will be conducted involving secondary schools to determine if the TCW-BI and/or provision of chilled water stations increase water consumption and effect changes in year 7 secondary students’ knowledge, attitudes or consumption of sugar sweetened beverages. Schools recruited to the study will be randomly allocated and non-blinded to one of four study arms. Students and members of the research team will not be blinded to group allocation. A blinded statistician not involved in the trial process will be responsible for final analysis.

### Sample size calculation

Power calculations were conducted to determine the sample size required to detect a change of 5% or more in the primary outcome, that being the proportion of students drinking 5 or more cups of water per day. Change was defined as the difference between the proportion at baseline, assumed to be 40% (as shown in the 2011 School Students Health Behaviour Survey [8]) and at final follow-up. The calculation assumed normality for the outcome, with alpha set at 5% and beta set at 20% [i.e. power at 80%]. In applying power calculations we took into account students being clustered in schools. Using these inputs and prior to an adjustment by design effect for correlated data, it was calculated that an effective sample of 761 students would be needed. Given an assumed intraclass correlation of 0.055 (calculated based on water consumption data from the NSW Schools Physical Activity and Nutrition Survey (SPANS) 2015) and an average school year 7 cohort of 135, this figure was then adjusted by a design factor of 8.37, thus putting the required number of students at 6370, being equivalent to 48 schools. Following adjustments for clustering at the school level (i.e. interclass correlation =0.055) and non-response (i.e. 20%), it was determined that a sample size of 60 schools was required.

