### Sample

All eligible schools within the boundaries of the three participating Local Health Districts will be invited to participate in the study, with the aim of recruiting 60 schools to the trial and randomly allocating 15 schools to each study arm. A sample of 60 schools will be selected from the three LHDs using a proportional stratified sampling technique. All year 7 students at recruited schools will be invited to participate. Schools that already have adequate working chilled water stations in situ (deemed to be one per 300 students) will be excluded from participating in the study. There is limited evidence regarding the ratio of chilled water stations per student, with the figure for this study being informed by guidance from US literature [15, 17, 18] and in consultation with the NSW Department of Education. Schools for special purposes for example schools for students with behavioural difficulties will be excluded from selection.

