#### Statistical analysis plan

Descriptive statistics will be used to summarise study variables. Categorical variables will be reported as counts and proportions. If normally distributed, continuous variables will be presented as means and standard deviations. Otherwise, they will be presented as medians and interquartile ranges.

Baseline characteristics of study arms will be compared to assess similarity at study entry, thereby allowing for the identification of significant imbalances requiring adjustment during analysis. If continuous, differences will be assessed using two-sample t-test or Mann-U Whitney tests for data with non-normal distributions. Categorical variables will be analysed by Pearson chi-squared tests or Fisher’s exact test.

To account for clustering at the LHD and school level and the capture of longitudinal data, multi-level regression models with mixed effects will be developed to estimate interventional effect. For each model building process, variables found to be significantly associated with the outcome measure in the univariable analysis at the 10% level will be retained in the final model. As the primary predictor of interest, intervention effect will be forced into the multivariable model in the form of 4-level categorical variable. Continuous outcome measures will be analysed using linear regression models. For binary outcome measures, analysis will be by binary logistic regression, while multinominal logistic regression will be used to analyse non-binary categorical measures. Diagnostic testing will be conducted on all models to ascertain validity. Each model will be tested for violations of model assumptions, existence of influential points and goodness of fit. Tests for all outcomes will be two-tailed, with levels of statistical significance set at 5%. Statistical analysis will be performed using Stata 15.0 (StataCorp LP, College Station, Texas) statistical software.

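### The 60-school sample size comes from a one-sample before-after calculation, so 80% power for a 5-point effect is not established for any randomised comparison

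*Protocol article*

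**What the plan says.** The Sample size calculation section of the protocol article sets out to "detect a change of 5% or more in the primary outcome", the proportion of students drinking five or more cups of water a day. The effect is a change over time: "Change was defined as the difference between the proportion at baseline, assumed to be 40" per cent, and the proportion at final follow-up. The error rates are "alpha set at 5% and beta set at 20% [i.e. power at 80" per cent. Sidedness is not given there, but the Statistical analysis plan section says "Tests for all outcomes will be two-tailed, with levels of statistical significance set at 5" per cent.

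From these inputs "it was calculated that an effective sample of 761 students would be needed". For clustering the section continues: "Given an assumed intraclass correlation of 0.055", with 135 year 7 students per school, giving a design factor of 8.37, 6370 students and 48 schools. A 20% allowance for non-response brings this to 60. The Sample section makes 60 the total for the trial, "randomly allocating 15 schools to each study arm".

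The Aim and Study design sections ask whether each intervention, alone or combined, changes water consumption under random allocation. The Statistical analysis plan section fits a multilevel longitudinal model with a four-level arm variable. The Discussion describes the factorial gain of using every school to assess each intervention.

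**The concern.** The calculation and the trial address different comparisons. The calculation asks whether one proportion, pooled over all schools including controls, has moved from an assumed 40%. The trial asks whether schools given an intervention differ from schools not given it. The second question involves two estimated proportions, each from part of the sample, and so has a much larger standard error.

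A pooled before-after change also cannot separate an intervention effect from a background trend. The Data collection section itself expects canteen availability of sweetened drinks to fall under a new state strategy.

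At stake is the stated power for the primary outcome. A reader who takes 80% at face value would give a non-significant result more weight against a 5-point effect than the design may justify.

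**Working it through.** **Inputs.** From the Sample size calculation section: 40% and 45%, alpha 0.05, power 0.80, intraclass correlation 0.055, 135 students per school, 20% non-response. From the Statistical analysis plan section: two-sided tests. From the Sample section: 60 schools, 15 per arm, hence 30 v 30 for each factorial main effect.

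**Reproducing the plan's figures.**
- One-sample formula: n = [1.96·√(0.40·0.60) + 0.8416·√(0.45·0.55)]² / 0.05² = 760.5, rounded up to 761. Exact match.
- Design effect: 1 + 134·0.055 = 8.37.
- Students: 761·8.37 = 6369.6, i.e. 6370.
- Schools: 6370/135 = 47.2, i.e. 48; then 48/0.8 = 60.

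**Other readings of 761.** A one-sided one-sample test gives 600. A two-group test gives 1,534 per group two-sided, or 1,208 one-sided. A paired before-after test gives 771 if a within-student correlation of 0.5 is assumed, which the article does not state. None of these matches, and the paired version is still uncontrolled. Nor can 761 be a per-group number, because the 60 schools derived from it are the trial total.

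**Two-group requirement.** n per group = [1.96·√(2·0.425·0.575) + 0.8416·√(0.24 + 0.2475)]² / 0.05² = 1533.3, i.e. 1,534. In total that is 3,068, about four times 761. For a main effect without baseline adjustment:
- If non-response is of students (108 per school, design effect 1 + 107·0.055 = 6.885): 1,534·6.885/108 = 97.8, i.e. 98 schools per level, 196 in total.
- If non-response is of schools: 2·1,534·8.37/135/0.8 = 237.8, i.e. 238 in total.

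**Power of the planned 60 schools, no baseline adjustment.** Effective n per side = schools·m/DE; SE = √(0.4875/effective n); power = Φ(0.05/SE − 1.96); detectable difference ≈ 2.80·SE. The article does not say whether the 20% is of students or of schools, so both are shown, with full response for reference.

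| Contrast | Basis | Effective n per side | SE (points) | Power for 5 points | Detectable (points) |
|---|---|---|---|---|---|
| Main effect | 30 v 30, m = 135 (full response) | 484 | 3.17 | 35% | 8.9 |
| Main effect | 30 v 30, m = 108 (student loss) | 471 | 3.22 | 34% | 9.0 |
| Main effect | 24 v 24, m = 135 (school loss) | 387 | 3.55 | 29% | 9.9 |
| Arm v control | 15 v 15, m = 135 (full response) | 242 | 4.49 | 20% | 12.6 |
| Arm v control | 15 v 15, m = 108 (student loss) | 235 | 4.55 | 19% | 12.8 |
| Arm v control | 12 v 12, m = 135 (school loss) | 194 | 5.02 | 17% | 14.1 |

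**With baseline adjustment.** SE is multiplied by √(1 − r²), where r is the correlation between a school's baseline and follow-up results. The article gives no r, so these values are assumptions, at 108 students per school:

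| r | Main-effect power | Main-effect detectable (points) | Arm v control power |
|---|---|---|---|
| 0.5 | 43% | 7.8 | 24% |
| 0.7 | 59% | 6.4 | 34% |
| 0.8 | 74% | 5.4 | 45% |
| 0.85 | 84% | 4.8 | 55% |

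For 80% power at 5 points the SE must be 5/2.80 = 1.78 points. For a main effect, r = √(1 − (1.78/3.22)²) ≈ 0.83. If 48 schools remain, r = √(1 − (1.78/3.55)²) ≈ 0.86.

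**The case against.** The strongest reply is that the unadjusted figures describe an analysis the protocol does not plan. The Statistical analysis plan section specifies longitudinal multilevel models, and the Data collection section links each student's surveys by an identifier. A comparison at follow-up alone is therefore nearer a lower bound than an estimate of the planned analysis. This stands, and it limits the conclusion.

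A reader might infer that 80% power is unattainable for every randomised comparison, or that the trial would probably miss a 5-point effect. The article does not support either statement for the main effects: assumed values of r give 59% at 0.7 and 84% at 0.85, and the true r is unknown. For arm v control, power stays below 50% for r up to 0.8. Nor does the article say that a null result would be taken to exclude 5 points; that is a risk in how the result is read.

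The 20% non-response is also open to two readings. The student-level reading gives 34% and 9.0 points, the school-level reading 29% and 9.9 points, so neither pair is fixed by the article.

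It might also be said that an article condenses a fuller protocol. That does not help here. The calculation is printed in full, takes no credit for baseline adjustment, and is for the wrong comparison. A later analysis plan cannot turn 761 into a two-group number.

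**Conclusion.** The point holds. The arithmetic from 761 to 60 schools is correct, but it sizes a pooled, uncontrolled before-after change and is used for a four-arm randomised trial. The 80% power for 5 points is not derived for any randomised contrast, and the stated inputs do not support it. On those inputs alone, power is about 29-35% for a main effect (detectable difference about 9-10 points) and about 17-20% for arm v control (about 12.6-14 points), depending on the non-response basis.

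What the planned model will achieve depends on an r that the article does not give. At 108 students per school, a main effect reaches 80% at r of about 0.83 or more, and arm v control does not reach it for r up to 0.85. These figures assume a normal approximation, equal school sizes and an intraclass correlation of 0.055 at follow-up.

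**What to change.** Keep the 60 schools and replace the sample size paragraph with a two-group, cluster-randomised calculation for the contrasts that randomisation supports.

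- Make the 30 v 30 main effects the sized comparison, and say how the model yields them: two factor terms, or marginal contrasts of the four-level arm variable. That variable does not give marginal effects by itself, so the calculation and the model must be tied together.
- Report separately the lower precision of arm v control and of the interaction. On the same basis the interaction's standard error is twice that of a main effect (2·3.22 = 6.4 points unadjusted at 108 per school).
- State whether the 20% non-response is of students or of schools.
- State the assumed r with its source. The article cites a survey for the intraclass correlation only and does not show that data on r exist; if none do, give a range.
- Report the resulting power or detectable difference, and withdraw the statement that 60 schools give 80% power for 5 points.

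The cost is a rewritten paragraph and a less favourable stated power. No schools or data items are added.

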### Setting

The study will be conducted in secondary schools (including non-private and private schools) that are within the boundaries of three NSW Local Health Districts (LHDs)(Central Coast, Illawarra Shoalhaven and South West Sydney LHDs). Two of these LHDs are similar in characteristics, which similar population demographics, distance from the hub of Sydney and numbers of secondary schools within them. The third LHD has a significantly higher population, greater diversity and a higher number of schools. To allow the study to progress within these settings ethical approval was obtained through the Hunter New England Human Research Ethics Committee (17/08/16/4.07), the NSW Department of Education (SERAP2017457) and Broken Bay, Sydney and Wollongong Catholic Diocese.

### Sample

All eligible schools within the boundaries of the three participating Local Health Districts will be invited to participate in the study, with the aim of recruiting 60 schools to the trial and randomly allocating 15 schools to each study arm. A sample of 60 schools will be selected from the three LHDs using a proportional stratified sampling technique. All year 7 students at recruited schools will be invited to participate. Schools that already have adequate working chilled water stations in situ (deemed to be one per 300 students) will be excluded from participating in the study. There is limited evidence regarding the ratio of chilled water stations per student, with the figure for this study being informed by guidance from US literature [15, 17, 18] and in consultation with the NSW Department of Education. Schools for special purposes for example schools for students with behavioural difficulties will be excluded from selection.

### Recruitment and study participation

An initial email sent to all eligible schools will inform them of the study. Schools responding to this email expressing interest in the study will be contacted via telephone/email to arrange a follow-up meeting. At this meeting schools will be fully informed of the study protocol, and provided with the study information and consent form. If the school wishes to participate in the study, school level consent will be gained by the principal providing signed consent. Participation of students in the evaluation component of the study will be through an opt-out consent process, where parents must provide written documentation to state they do **not** wish their child to participate in the evaluation (except in Catholic schools within one Catholic Diocese, where an opt-in process will be mandatory).

Simple random sampling will be used to select from the pool of consenting schools, the requisite number of schools within each LHD required for inclusion in the study. Once 60 schools are identified for the study sample randomisation of the schools to the study arms will take place. Schools will be randomised by the study statistician using a computerised random number generator. Subsequently, principals will be informed of which study arm they have been allocated to. Those who were not included in the study sample will be informed of this. Following randomisation, baseline measures will be taken, interventions implemented and post and follow-up data collected as per Fig. 1 Flowchart of the study.

